#### 2.9.1 MRI acquisition and planned analysis

MRI scans will be acquired using a 3.0T MRI scanner (MAGNETOM Prisma MRI scanner, Siemens Healthcare, Erlangen, Germany) equipped with a 64-channel head-and-neck coil. The MRI protocol includes the following sequences: (a) T2-weighted turbo spin-echo (TSE) [matrix 448 × 448, FOV 220 × 220 mm^2^, 29 transversal slices, slice thickness 4 mm, repetition time (TR) = 3,490 ms, echo time (TE) = 95 ms, acquisition time 2 min 42 s], during which participants will be asked to keep their eyes closed, not to think about anything in particular and not to fall asleep; (b) a fast fluid-attenuated inversion recovery (FLAIR) [matrix 240 × 256, FOV 240 × 256 mm^2^, 176 sagittal slices, slice thickness 1 mm, TR = 8,000 ms, TE = 314 ms, inversion time (TI) = 2,350 ms, acquisition time 7 min 54 s]; (c) T1-weighted multi-echo MPRAGE sequence (MEMPRAGE) [matrix 256 × 256, FOV 256 × 256 mm^2^, 176 sagittal slices, slice thickness 1 mm, TR = 2,500 ms, TE = 1.67/3.48/5.29/7.10 ms, TI = 1,080 ms, flip angle 8°, acquisition time 7 min 27 s]; (d) T2-weighted “hippocampal dedicated” coronal scan with 0.4 × 0.4 × 2.0 mm^3^ resolution, partial brain coverage and oblique orientation as described by Yushkevich et al. (2015).

Regarding whole-brain functional connectivity, connectomics changes after intervention will be investigated between pairs of regions of the whole brain (with particular interest in areas mainly involved in training-related cognitive processes) and in the global and local topological properties of large-scale networks through graph theoretical approach.

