In light of the foregoing, this study aims to evaluate the effectiveness of an immersive virtual-reality (IVR) and telemedicine-based multi-component intervention, combining cognitive training and a health and lifestyle education program, on objective and subjective cognitive function, psychiatric symptoms, quality of life and brain connectivity in older adults at high-risk for cognitive decline and dementia (i.e., SCD). The primary objective is to determine whether the multi-component intervention, when compared to an active control condition, leads to significant post-intervention gains in objective cognitive functioning, and whether these gains are greater than those induced by a cognitive-only condition. The secondary objectives are: (1) to assess the transfer effect of the intervention on self-perceived cognitive functioning, psychiatric symptoms and quality of life; (2) to assess intervention-induced changes in whole-brain functional connectivity, as highlighted by resting state-fMRI images; (3) to assess user compliance with telemedicine approach combined with IVR. Exploratory objectives include: (1) investigating potential moderators of intervention efficacy (e.g., demographics, cognitive reserve, SCD severity, lifestyle and dementia risk factors); and (2) evaluating hypotheses regarding neuroimaging results and their association with behavioral data (e.g., correlation between behavioral and imaging data, association between post-training brain changes and participants' characteristics, and whether intervention-induced improvements rely on specialized brain areas or depend on compensatory responses from other regions).

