Secondary outcomes include the evaluation of intervention-induced changes in: (a) Subjective memory functioning, using Subjective Memory Complaints Questionnaire (De Simone et al., 2023b) and Multifactorial Memory Questionnaire (Raimo et al., 2016); (b) Psychiatric symptoms, using Beck Depression Inventory (BDI; Beck et al., 1961) and State–Trait Anxiety Inventory (STAI; Spielberger, 1983); (c) Quality of Life and Health status, using Short Form-36 Health Survey (Apolone and Mosconi, 1998) and Patient Global Impression of Change—PGIC (Hurst and Bolton, 2004); (d) Whole-brain functional connectivity.

Additionally, participants will be asked to complete the following questionnaires during the post-training evaluation (T1) in order to assess the acceptance, usability, and feasibility of the proposed IVR and telemedicine-based program: Simulator Sickness Questionnaire (Kennedy et al., 1993), User Satisfaction Evaluation Questionnaire (Gil-Gómez et al., 2017), Nasa Task Load Index (Hart and Staveland, 1988), User Experience Questionnaire (Laugwitz et al., 2008) and a modified version of the System Usability Scale (Brooke, 1995; Grier et al., 2013) that also includes an open question for qualitative input about users' experience.

For further exploratory analyses, we will additionally collect measures of cognitive reserve by means of the Cognitive Reserve Index questionnaire (Nucci et al., 2012) and dementia risk factors by adapting in Italian several items of the Lifestyle for Brain Health (Schiepers et al., 2018), in order to evaluate the potential impact of underlying mechanisms on the efficacy of intervention. Data related to participants' performance on the IVR cognitive tasks (e.g., accuracy, timing), which will be collected through the telemedicine platform for each individual at-home training session, will be also considered for analyses.

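### The MRI section lists only structural sequences and attaches the resting instruction to a structural T2 scan, which contradicts the resting-state connectivity outcome

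*Protocol article*

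**What the plan says.** Section 1 (Introduction) gives as its second secondary objective "to assess intervention-induced changes in whole-brain functional connectivity, as highlighted by resting state-fMRI images". Section 2.5 (Outcome measures) repeats it as the last of four lettered secondary outcomes, "d) Whole-brain functional connectivity". Section 2.1 places a 3T scan before and after the intervention for those participants in whom it can be done.

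Section 2.9.1 then describes the acquisition. Its list opens with "The MRI protocol includes the following sequences: (a) T2-weighted turbo spin-echo (TSE" and runs on without a gap to (d): FLAIR, a T1 multi-echo MPRAGE, and a T2 scan dedicated to the hippocampus that covers only part of the brain. Item (a) carries the parameters "matrix 448 × 448, FOV 220 × 220 mm^2^, 29 transversal slices, slice thickness 4 mm" and "repetition time (TR) = 3,490 ms, echo time (TE) = 95 ms, acquisition time 2 min 42 s", followed directly by the clause "during which participants will be asked to keep their eyes closed, not to think about anything in particular and not to fall asleep". The next paragraph of the section plans analyses of connectivity between pairs of brain regions and of network topology by graph theory.

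**The concern.** Functional connectivity is computed from how the signal in different regions varies together over time, so it needs a functional time series covering the whole brain. Section 2.9.1 names no such acquisition, and no other section of the article does. The section also makes a positive misstatement: the instruction that belongs to a resting-state run is given for an anatomical scan.

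The objective, the outcome and the analysis paragraph therefore rest on data that the listed sequences do not produce. If the scanner set-up really matches the list, the connectivity outcome has no data, and a baseline functional scan cannot be obtained once a participant has been trained. If the set-up does contain the run, the published protocol still misidentifies the scan during which participants rest and does not name the scan on which the outcome depends.

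**Working it through.** The article states no figure that needs reproducing. The check sets the required data against the listed sequences, with simple arithmetic on item (a) to see whether it could be a mislabelled resting-state run.

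**Required** (sections 1, 2.5 and 2.9.1, second paragraph): a whole-brain functional time series before and after the intervention.

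**Listed** (section 2.9.1, first paragraph):

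| Item | Sequence | Type | Whole-brain time series? |
|---|---|---|---|
| (a) | T2 turbo spin-echo | structural | no |
| (b) | FLAIR, inversion time 2,350 ms, 1 mm sagittal slices | structural | no |
| (c) | T1 multi-echo MPRAGE, inversion time 1,080 ms, 1 mm sagittal slices | structural | no |
| (d) | T2 hippocampal, partial coverage | structural | no |

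Functional sequences listed: 0 of 4.

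**Could item (a) be the resting-state run under a wrong name?** Inputs are the printed parameters in section 2.9.1.

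- Duration: 2 × 60 + 42 = 162 s.
- Repetition periods: duration / TR = 162 / 3.49 = 46.4.
- In-plane resolution: field of view / matrix = 220 / 448 = 0.49 mm.
- Slice coverage: 29 × 4 mm = 116 mm, without any gap.

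A turbo spin-echo sequence uses its repetition periods to build up one set of images; it does not produce a new volume in each period. A 448 × 448 matrix at 0.49 mm with an echo time of 95 ms, completed in about 46 periods, fits a single anatomical T2 volume. The parameters agree with the printed name, so the misplaced element is the instruction and not the label of the scan.

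**What depends on the missing run.** One of the four lettered secondary outcomes in section 2.5 depends on it entirely. Exploratory objective 2 in section 1 depends on it in part: it speaks of imaging data and post-training brain changes in general, and structural scans at both visits could serve some of that.

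**The case against.** The strongest reply is that this is a reporting slip. Section 1 names resting-state fMRI outright, section 2.9.1 contains the standard resting instruction and a connectivity analysis plan, and the list is introduced by a verb of inclusion that need not be exhaustive. The instruction looks like what remains of a dropped list item. The trial is already under way (section 3), and acquisition times printed to the second suggest that the article describes an existing scanner set-up. This stands. A reader might infer that no functional scan is being acquired and that the outcome is lost for every participant; the article does not support that.

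A second reply is that a journal article condenses. Item (d) itself gives no TR, TE or duration and refers to a cited source. This stands in part: missing parameters alone would not be a finding. It does not excuse leaving out the one scan that a named outcome needs while giving detailed parameters for three others, and it does not explain an instruction placed on the wrong scan.

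Third, a reader might conclude that exploratory objective 2 falls as a whole, or that the full sample is affected. Neither follows. That objective is not confined to functional data, and section 2.1 never planned MRI for participants in whom it cannot be done.

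**Conclusion.** The article contradicts itself. Sections 1 and 2.5 and the second paragraph of section 2.9.1 require resting-state functional data; the sequence list in section 2.9.1 contains none and assigns the resting instruction to a structural scan. As written, the listed protocol yields no data for secondary outcome (d), one of four, or for the connectivity-dependent part of exploratory objective 2.

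The conclusion concerns the text. It assumes that the list in section 2.9.1 is what a reader would take as the acquisition protocol. It does not establish what the scanner runs, and a drafting omission is the more likely explanation. An irrecoverable loss of baseline data arises only if the run is in fact absent. The primary outcome, the sample size and the primary comparison are untouched.

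**What to change.** 1. Check the scanner protocol now in use for a resting-state functional run at both visits.
2. If it is there, add it by name to the list in section 2.9.1 with its key acquisition parameters (TR, TE, voxel size, number of volumes, duration), and move the resting instruction from the T2 turbo spin-echo to that run. The cost is one corrected paragraph.
3. If it is not there, add it to the existing MRI visit before any further baseline scans, by amendment, and state that connectivity change can be assessed only in participants with a functional baseline scan. The cost is some added time in a visit that already takes place, plus the amendment. The analysis need not be restricted to participants with both scans, since section 2.9 allows linear mixed models, which can use incomplete pairs.
4. If the run cannot be added, withdraw the connectivity outcome and its analysis paragraph, and limit exploratory objective 2 to what the structural scans can support.

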## 3 Discussion

There is an urgent need to develop population-level, low-cost interventions that will reduce the risk of cognitive decline and dementia. In this framework, we are currently carrying out the present RCT study to evaluate the effects of a novel immersive virtual reality and telemedicine-based multi-component intervention focused on specific cognitive functions (i.e., long-term associative memory, working memory binding, spatial pattern separation) and education program in individuals with subjective cognitive decline. In fact, it has been widely demonstrated that SCD is a condition at high risk for cognitive decline and clinical progression in dementia (Jessen et al., 2020).

The design of this study has many strengths with respect to previous interventions described in the literature. These strengths include the targeted cognitive training approach, the multi-component nature of the intervention, the use of immersive virtual reality, and the telemedicine method.

The first relevant point is the development of a cognitive training specifically designed and adapted to the cognitive difficulties of individuals with SCD. Recent findings suggest that self-perceived cognitive decline complained by SCD, but as yet undetectable using the traditional neuropsychological tests, actually reflects objective alterations affecting specific and more demanding processes (e.g., associative learning and recall, working memory binding, pattern separation processes; De Simone et al., 2023b; Kormas et al., 2020; Markova et al., 2023). Accordingly, one possible way to improve the efficacy of cognitive interventions in SCD, and thus produce more robust and broadly generalizable effects compared to previous results in the literature, may be to target specific cognitive processes, as those that have been found precociously and objectively compromise in SCD (e.g., associative memory for face-name associations) rather than more general cognitive functions (e.g., word list recall). To the best of our knowledge, only one study tested the efficacy of memory training that targets specific cognitive processes in SCD (i.e., memory for face-name associations) showing promising results (Pike et al., 2018). However, this finding is limited by some methodological shortcoming (e.g., single-session training, no RCT design) and thus more evidence is still needed.

The second point of strength is the multi-component nature of the intervention. As reported in the introduction, up to 40% of dementia cases could be prevented by acting on several modifiable risk factors, including lifestyle factors as cognitive activity, physical exercise and dietary habits (Livingston et al., 2020). The implementation of interventions targeting multiple dementia risk factors simultaneously can thus represent an effective strategy to increase efficacy. Health-related education and lifestyle interventions aimed at improving brain health and cognitive functioning before the onset of dementia have demonstrated overall positive effects on both subjective and objective cognitive function in healthy older people and in individuals with SCD (Sheng et al., 2020; Cohen-Mansfield et al., 2015). Thus, combining cognitive training with lifestyle modification programs could potentially result in more beneficial effects on cognitive, behavioral, and psychological functioning compared with interventions focusing only on a single component.

From a technological point of view, another point of strength is the implementation of the intervention in immersive virtual reality (IVR). A well-known obstacle in the field of cognitive interventions is the generally poor evidence for transfer effects of cognitive improvement to outcomes related to patients' daily living (Willis and Belleville, 2016). Another potential issue is a lack of motivation to participate in the assigned training, which is often affected by low pleasantness and attractiveness of the activities to be carried out. These problems probably contribute to attrition rates that are often high in training programmes (Willis and Belleville, 2016). IVR has been suggested as a feasible solution to accommodate these issues because it offers a more ecological environment for training activities that can simulate events that individuals might encounter in their daily lives, and with which they can interact in a naturalistic way by using their own bodies. This could result in a larger transfer effect (Tieri et al., 2018). Moreover, IVR has proven to induce the sense of presence (i.e., illusion to be in the virtual space which allows eliciting realistic reactions to virtual stimuli) and thereby increase engagement, motivation and the feeling of entertainment in users (Tieri et al., 2018; Sanchez-Vives and Slater, 2005; Fusco and Tieri, 2022); this could, in turn, result in reducing attrition rates in training programs. Despite the extended recent interest in the use of IVR for cognitive rehabilitation across several psychiatric and neurological disorders, including mild cognitive impairment and dementia (Jahn et al., 2021; Ren et al., 2024), this field is still unexplored in SCD. To the best of our knowledge, only one study to date has tested the efficacy of IVR cognitive training in SCD (Kang et al., 2021), reporting promising results.

A final point of note is the use of a telemedicine approach. Compared with traditional in-person interventions, in fact, the implementation of intervention that people can perform directly at their own homes by using a new generation of virtual reality HMD remotely controlled in real-time could represent an important step forward for distance treatment and a valuable contributor in improving the continuity of care. In fact, its cost-effectiveness, accessibility, flexibility, and comprehensiveness make it an ideal option for individuals unable to attend outpatient appointments due to various barriers such as work, distance, transportation issues, or disability. While recent reviews have demonstrated the effectiveness and feasibility of telerehabilitation for cognitive function in individuals with mild cognitive impairment and dementia (De Simone et al., 2023a; Cotelli et al., 2019; Costanzo et al., 2020), research on its application for subjective cognitive decline remains limited.

In the evaluation of the intervention and its possible effectiveness, some potential critical aspects and open issues should be also considered. The first regards technological expertise: it is more common for older individuals to show limited familiarity with the technology and may, therefore, have difficulties in using VR devices and managing the related software. However, we believe that the in-person training provided prior to the intervention, together with guaranteed technical support throughout its duration, could be useful for mitigating this negative effect.

Second, IVR has been related to cybersickness, a phenomenon often experienced with immersive VR environments. It typically manifests through adverse symptoms such as nausea, dizziness, headaches, and disorientation. Nevertheless, a recent systematic review of immersive VR studies conducted with elderly individuals indicated a minimal occurrence and low symptom ratings for cybersickness (Bauer and Andringa, 2020). Anyway, this aspect will be carefully examined through the analysis of data from the Simulator Sickness Questionnaire (Kennedy et al., 1993), as well as participants' qualitative reports, to thoroughly assess the intervention's usability and feasibility. Finally, and particularly relevant for at-home unsupervised interventions, is the issue of treatment adherence. Maintaining consistent engagement can be challenging outside of a controlled clinical environment. Our telemedicine approach, which includes scheduled virtual check-ins and remote monitoring functionalities, is specifically designed to explore strategies for supporting and improving adherence in this context. By examining participation rates, completion of assigned tasks, and qualitative feedback, our research aims to shed light on how remote support can influence long-term engagement and sustainability, addressing a critical open question in the management of these types of interventions.

In summary, the results of this randomized controlled trial will provide crucial evidence regarding the effectiveness of a novel multi-component intervention, integrating cognitive training and health education delivered via immersive virtual reality and telemedicine, for individuals at high risk of cognitive decline and dementia (SCD). Given its relatively low cost and accessibility, this approach has the potential to significantly contribute to primary prevention and early cognitive rehabilitation efforts aimed at reducing dementia risk.
